### Trial design {12}

This study is a randomized, controlled, parallel-group clinical trial. Participants will be randomly allocated in a 1:1 ratio to either the control or immersive VR intervention group. Allocation will be conducted by an external researcher uninvolved in recruitment or intervention delivery, and data analysts will be blinded to group assignments. The trial investigates the effects of immersive VR on exercise tolerance in hospitalized heart failure patients, aiming to generate foundational evidence to support the use of immersive technologies in cardiac rehabilitation.

## Methods: participants, interventions and outcomes

### Trial setting {13}

The study will be conducted on inpatient units in the Cardiology and Cardiac Surgery departments of Hospital São Paulo, São Paulo, Brazil. This referral hospital provides infrastructure for monitoring patients during interventions, including a qualified multidisciplinary team and all resources necessary to ensure participant safety and well-being.

### Superiority design justification

This trial uses a superiority design rather than a non-inferiority or equivalence design, based on the following rationale:Expected clinical advantage: The theoretical framework (attentional distraction, increased motivation) and preliminary data suggest immersive VR may provide benefits above standard exercise. The key research question is whether VR is superior to standard exercise for improving exercise tolerance.No defined non-inferiority margin: There is no established margin for what constitutes a clinically meaningful non-inferiority threshold for exercise tolerance in this clinical setting. Superiority trials are recommended when such margins are unavailable or unvalidated.Ethical and safety reasons: If immersive VR were inferior to standard exercise (i.e. associated with reduced exercise tolerance or safety issues), this finding would be critical for patient care and adoption decisions. Non-inferiority designs are more suitable once basic superiority and safety are clarified for novel interventions in vulnerable populations.

Should VR demonstrate superior outcomes, future research may consider non-inferiority or equivalence approaches for broader implementation, or explore subgroup effects.

### Characteristics of the people who are needed for the trial

**Table Taba:** 

**Characteristic**	**The people we would expect to see included**
Age	Adults aged ≥ 18 years Data to be collected and reported: ● Mean age (years) ● Median age (years) ● Standard deviation ● Range (minimum and maximum age) ● Age distribution by group (intervention vs. control)
Sex	● All sexes eligible ● Data collection method: Self-reported biological sex ● Categories: Male, Female, Intersex
Gender	● All gender identities ● Data collection method: Optional self-report during informed consent process ● Categories to report: Man, Woman or any other gender identities as reported by participants
Race, ethnicity and ancestry	● All races and ethnicities ● Data collection method: Self-reported using Brazilian census categories Categories used (Brazilian IBGE classification): o White o Black o Brown/Mixed race o Asian o Indigenous o Did not declare
Socioeconomic status	● All socioeconomic backgrounds ● Data collection method: Self-reported during baseline assessment ● Socioeconomic indicators to collect: o Education level: Primary education, Secondary education, University degree, Postgraduate degree, No formal education o Employment status: Employed full-time, Employed part-time, Unemployed, Retired, Informal work, Unable to work due to illness o Health insurance type: Public (SUS—Unified Health System), Private health insurance, Both public and private
Geographic location	● Study setting: Single-center urban hospital in Brazil ● Recruitment location details: o Country: Brazil o City: São Paulo o Institution: Hospital São Paulo (Federal University of São Paulo—UNIFESP) o Clinical units: Inpatient Cardiology Unit and Cardiac Surgery Unit
Other characteristics relevant to the trial	● Clinical diagnosis of HF with left ventricular ejection fraction (LVEF) ≤ 50% confirmed by echocardiography

### Eligibility criteria for participants {14a}

#### Inclusion criteria

Clinical diagnosis of HF with left ventricular ejection fraction (LVEF) ≤ 50% confirmed by echocardiography.Men and women aged ≥ 18 years.Hemodynamic stability for the previous 48 h: no malignant ventricular arrhythmias; no complex extrasystoles; no supraventricular/sinus tachycardia > 120 bpm; no second- or third-degree atrioventricular block; and no signs of low output.New York Heart Association (NYHA) Functional Class I–IV (all functional classes included)Medical clearance for rehabilitation.Provision of written informed consent.

#### Non-inclusion criteria

Arrhythmias that contraindicate physical exertion.Unstable angina.Acute myocardial infarction or cardiac surgery in the previous 6 months.Advanced or terminal cancer with life expectancy < 3 months (per physician)Cancer-related symptoms preventing safe exercise: severe fatigue, cachexia, uncontrolled pain (≥ 5/10 at rest), dyspnea at rest or other cancer complications as determined by the investigator.

#### Exclusion criteria

Fever in the previous 48 h, with leukocytosis and/or elevated C-reactive protein.Conditions limiting VR use, specifically: significant visual deficit, cognitive impairment, psychiatric or neurological disorders or history of photosensitive epilepsy.Orthopedic or neurological conditions precluding safe cycle-ergometer use.

### Eligibility criteria for sites and those delivering interventions {14b}

#### Study site

This trial will be conducted at the Cardiology Division, Hospital São Paulo, Federal University of São Paulo (UNIFESP), São Paulo, Brazil.

#### Physiotherapist qualification

The exercise intervention will be delivered by a licensed physiotherapist employed by Hospital São Paulo who is registered with CREFITO (Regional Physical Therapy Council, Brazil), experienced in cardiac rehabilitation and holds valid CPR certification.

#### Standardized institutional protocols

The exercise protocol and vital signs monitoring procedures are identical to institutional standard protocols already in routine use at Hospital São Paulo’s Cardiology Division. The physiotherapist will be trained and accustomed to cycle ergometer operation, Modified Borg RPE assessment, vital signs measurement, electrocardiogram (ECG) monitoring and standard exercise termination criteria. This standardization ensures consistency and minimizes variability in exercise delivery and monitoring across all study sessions.

#### VR-specific training

The only intervention difference between groups is the immersive VR addition. VR training includes Meta Quest 2 operation, VZfit functionality, participant guidance, VR-specific safety procedures and concurrent monitoring coordination. The physiotherapist will practice VR delivery before participant enrolment; training documentation will be maintained.

#### VR protocol standardization

The VR intervention will be delivered following standardized procedures to ensure consistency across all participants. The physiotherapist will receive training on VR delivery protocols, including proper equipment setup, participant guidance and safety procedures. All VR sessions will adhere to a consistent protocol with standardized participant instructions and identical intervention parameters to minimize variability between sessions.

#### Data collection quality control

Standardized data collection forms will be used for all measurements. Critical measurements will be recorded in real-time. Monthly team meetings will review exercise logs and data completeness; discrepancies will be discussed and addressed.

### Study supervision and oversight

All interventions will be supervised by the Senior Investigator, [name] [name].

### Who will take informed consent? {32a}

Informed consent will be obtained by trained members of the research team, specifically the Principal Investigator ([name] [name]) or designated research coordinators trained in Good Clinical Practice (GCP) and the study protocol.

The informed consent form will detail all relevant study information, including: trial objectives, procedures, expected duration of participant involvement, potential risks and benefits, confidentiality protections and voluntary nature of participation. The form will be provided to participants (or their legal representatives if applicable) in Portuguese, allowing sufficient time for review and questions before written consent is obtained.

Participants will have the opportunity to ask questions and discuss any concerns with the research team before deciding whether to participate. Participation is entirely voluntary, and participants may withdraw at any time without affecting their standard clinical care or treatment at the institution.

All informed consent procedures will be conducted and overseen by the Research Ethics Committee of UNIFESP to ensure compliance with Brazilian regulations (CONEP—National Research Ethics Commission), the Declaration of Helsinki and International Council for Harmonisation (ICH) guidelines for research involving human participants.

### Additional consent provisions for collection and use of participant data and biological specimens {32b}

No additional informed consent for ancillary studies is required. This trial does not include collection of biological specimens beyond clinical assessments performed as part of standard monitoring during the exercise session. Data collection is restricted to variables related to the intervention and monitoring of clinical and physical performance parameters (vital signs, perceived exertion, exercise duration). Participants will be informed during the initial consent process that data may be used for future research related to VR and cardiac rehabilitation; specific consent for future ancillary studies will be obtained separately if undertaken.

### Intervention and comparator description {15a}

#### Intervention group: immersive VR cycle-ergometer exercise

##### Overview

Participants will complete a single supervised aerobic exercise session on a stationary cycle ergometer while wearing an immersive VR headset (Meta Quest 2), providing real-time visual and audio feedback synchronized with pedaling.

##### VR environment

Application: VZfit (VirZOOM Inc.) for Meta Quest 2Standardized Route: Pre-recorded scenic outdoor cycling route (countryside landscape with gentle terrain variation). All intervention participants experience the identical VR route to minimize environmental preference variabilityRoute options: Same scenic route available in daytime or nighttime ambianceSynchronization: Virtual avatar movement synchronized in real-time with participant pedaling speed; participants observe avatar progress through the virtual landscapeAudio: Ambient nature sounds (wind, birds chirping, nature soundscape) corresponding to virtual setting; no music to avoid independent motivational confoundingInteractivity: Virtual environment responds to pedaling cadence, providing real-time visual feedback of progress

##### VR familiarization

Headset fitting and display adjustment (~ 1 min): Proper fit, comfort verification, interpupillary distance (IPD) calibration, head strap tensionOrientation to virtual environment (~ 2 min): Participant views VR environment while stationary; guided tour of the virtual settingMovement practice (~ 30–60 s): Participant pedals at low intensity while observing synchronized avatar movementComfort and safety assessment: Supervising physiotherapist assesses for any discomfort, dizziness or nausea; session proceeds only if participant comfortableSafety procedures reviewed: Emergency exit procedures, communication methods and participant controls explained

Participants experiencing significant discomfort during familiarization will not proceed to the exercise protocol.

##### Session delivery

Delivered by: Trained physiotherapist employed at Hospital São PauloTiming: Daytime hours (08:00–16:00); consistent time of day for each participant to minimize circadian variabilitySingle session: Only one exercise session per participantReal-time monitoring: Continuous observation for symptoms or hemodynamic changesMeasurement timing: Vital signs and RPE recorded every minute during exercise and at recovery

#### Control group: standard cycle-ergometer exercise

##### Overview

Participants will complete an identical exercise protocol to the intervention group, with the exception that no VR headset will be worn. Exercise occurs in the standard hospital room environment.

##### Exercise protocol

Identical to intervention group:Same cycle ergometer equipment and resistance settingsSame exercise structure (5 × 3-min active blocks, 1-min rest intervals)Same total duration (up to 20 min)Same intensity prescription (self-selected cadence, RPE-guided, target RPE 3–4)Same monitoring procedures (vital signs every minute, RPE every minute, real-time cadence recording)Same session termination criteriaSame physiotherapist supervision

Differences from intervention group:NO VR headset wornStandard hospital room environment (windows, walls, standard ambient hospital sounds)Standard cycle ergometer display showing time, cadence, estimated work (no virtual avatar or scenic environment visual)

##### Session delivery

Timing: Same time of day and conditions as intervention groupReal-time monitoring: Identical vital signs, RPE and observation protocolsTermination criteria: Identical to intervention groupPost-exercise: Identical to intervention group (recovery, assessment, discharge)

#### Only difference: presence or absence of immersive VR technology

This active comparator design isolates the specific effect of VR immersion while controlling for all other exercise-related variables, allowing any observed differences in primary and secondary outcomes to be validly attributed to the VR intervention itself rather than differences in exercise prescription, supervision or monitoring.

#### Single-session design rationale

Single-session design was chosen for scientific and pragmatic reasons: (1) permits precise control over confounding variables (circadian effects, medication timing, rapidly changing clinical status); (2) demonstrates immediate physiological feasibility in a controlled setting, essential groundwork for future multi-center longitudinal studies; (3) minimizes resource demands in acute care settings with limited VR availability (Fig. 1).

**Fig. 1 Fig1:**
[figure not shown]
Schematic of the aerobic exercise protocol performed in the control and intervention groups

### Criteria for discontinuing or modifying allocated intervention/comparator {15b}

Exercise will be discontinued immediately if any of the following occur:

#### Participant-initiated discontinuation

Perceived dyspnea or lower-limb fatigue ≥ 5 on Modified Borg Scale (indicating excessive effort)Participant requests to stop due to discomfort, inability to continue or any other reasonAdverse effects related to the VR device compromising well-being, requiring suspension

#### Hemodynamic and electrocardiographic discontinuation

Participants will be continuously monitored using sphygmomanometer, pulse oximetry, ECG and heart rate monitor. Exercise will be terminated immediately if any of the following occur, in accordance with the Brazilian Society of Cardiology’s 2024 Ergometry Consensus [23]:

#### Blood pressure abnormalities

Diastolic blood pressure (DBP) > 120 mmHg in normotensive patients or > 140 mmHg in hypertensive patientsPersistent drop in systolic blood pressure (SBP) ≥ 10 mmHg below baselineMarked rise in SBP > 200 mmHg

#### Heart rate abnormalities:

Heart rate > 130 bpm or < 40 bpmAbnormal decrease in heart rate relative to exercise effort

#### Electrocardiographic abnormalities

ST-segment depression ≥ 1 mm or ST-segment elevationMalignant arrhythmias (bigeminy, trigeminy, sustained ventricular tachycardia, atrial fibrillation with rapid ventricular response)

#### Clinical manifestations

Chest discomfort or painAtaxia, dizziness, pallor or cyanosisPresyncope or syncopeDyspnea disproportionate to effort (Modified Borg ≥ 5)

#### VR-system issues (intervention group)

Intolerance to the VR system compromising participant well-being (severe nausea, visual discomfort, severe dizziness)

#### Technical failure

Failure of monitoring systems (ECG, vital signs measurement) during intervention

#### Post-discontinuation protocol upon immediate discontinuation

Remove VR headset (intervention group only)Continue ECG monitoring for minimum 5 minAssess vital signs and symptomsProvide rest and recovery periodDocument reason for discontinuation

The study will take place in a hospital environment with immediate medical support. All sessions will be supervised by trained professionals to ensure safety and well-being throughout the intervention. These discontinuation criteria apply identically to both intervention and control groups.

### Strategies to improve adherence to intervention/comparator {15c}

Adherence is promoted through comprehensive participant engagement: detailed informed consent integrated into routine clinical care with emphasis on study contribution to cardiac rehabilitation science and minimal burden (single session). During exercise, continuous physiotherapist supervision provides real-time guidance, encouragement and safety oversight. The VR group benefits from a structured 5-min familiarization process minimizing technology anxiety, an immersive scenic virtual environment with synchronized avatar movement providing biofeedback.

Post-exercise, participants receive immediate feedback on total exercise time, positive reinforcement and PACES/SUS questionnaires administered while experience is fresh. Study purpose is communicated emphasizing potential benefit to future heart failure patients. For this single-session design, adherence encompasses participant attendance and protocol completion while maintaining safety, comfort and sense of agency.

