### Outcomes {16}

#### Primary outcome

Influence of VR on tolerance to cycle-ergometer aerobic exercise in hospitalized patients with HF. The primary endpoint is effective exercise time (minutes), defined as total session duration until interruption due to physical limitations or symptoms, comparing VR vs. no-VR.

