#### Harms monitoring and safety procedures

##### Real-time monitoring during exercise

The supervising physiotherapist has authority to terminate the exercise session immediately if any safety concern arises. Medical support is available immediately if needed, with emergency equipment accessible per hospital protocol. Participants have the explicit right to request session termination at any time for any reason, without penalty or compromise to clinical care.

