**POST-EXERCISE ASSESSMENTS**				
Total exercise time (minutes) (g)				X
Recovery vital signs				X
SUS—VR group only (i)				X
PACES (h)				X
Adverse events assessment (j,k)				X

a) Single-session design: Only ONE exercise session per participant during hospitalization.

b) Timepoints: Enrollment → Randomization → Intervention → Post-Exercise/Close-Out. No follow-up.

c) Both groups identical protocol except: VR group receives immersive VR headset; control group receives standard cycle ergometer.

d) Hospital Anxiety and Depression Scale (HADS): 14-item self-report questionnaire assessing anxiety (7 items, score 0–21) and depression (7 items, score 0–21) during acute hospitalization [24, 25]

e) Continuous vital signs monitoring: Blood pressure (BP, mmHg, systolic/diastolic), heart rate (HR, bpm), peripheral oxygen saturation (SpO₂, %) and respiratory rate (RR, breaths/min) recorded every minute throughout exercise and recovery period via automated monitors and continuous 12-lead ECG.

f) Session termination criteria: Immediate termination triggered if Rating of Perceived Exertion (RPE) ≥ 5 (‘hard’ intensity) OR if any safety threshold exceeded: BP > 200 mmHg or < 80 mmHg (systolic), HR > 130 or < 40 bpm,SpO₂ < 85% or ST-segment changes on ECG.

g) Total exercise time: Cumulative pedaling time (minutes) from initiation to termination.

h) Physical Activity Enjoyment Scale (PACES): 18-item questionnaire (score 18–80); higher = greater enjoyment [18, 19]

i) System Usability Scale (SUS10-item questionnaire (score 0–100); ≥ 68 indicates above-average usability; ≥ 70 considered acceptable for clinical implementation [20, 21]

j) Adverse events: Serious (requiring intervention) vs. non-serious. Documented immediately post-exercise.

k) Real-time data collection: All vital signs, RPE, observations recorded by physiotherapist on paper CRF during exercise; transferred to REDCap same day.

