### Assignment of interventions: blinding

#### Who will be blinded {24a}

##### Blinding limitations

Due to the nature of the VR intervention, participants and the physiotherapist cannot be blinded. Participants will necessarily be aware of whether they are receiving standard exercise or VR-augmented exercise, as the presence or absence of the immersive VR headset is inherently visible. Similarly, the physiotherapist delivering the intervention must know group allocation to deliver the assigned intervention appropriately.

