##### Measures to minimize bias

Despite the lack of participant and intervention provider blinding, bias will be minimized through the following strategies:Objective measurement standardization: Vital signs and exercise duration will be recorded using calibrated, automated monitoring equipment in real-time, reducing observer bias in physiological measurements.Standardized procedures: All participants in both groups will receive identical exercise protocols, duration, intensity monitoring procedures and standardized verbal instructions, ensuring that measurement procedures are equivalent across groups.Data analyst blinding: Statistical analyses will be conducted by an external biostatistician using blinded data coding (Group A/Group B only), without knowledge of intervention group assignment during analysis to prevent analysis bias.Allocation concealment: Participants and clinical staff will not know group assignment until after baseline assessments are completed.

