### Data collection and management

#### Plans for assessment and collection of outcomes {25a}

Data will be collected by trained physiotherapist who will supervise all exercise sessions and record data using standardized case report forms (CRF). Patient-reported satisfaction with the exercise experience will be assessed using the Physical Activity Enjoyment Scale (PACES) [18, 19], a 18-item self-report questionnaire administered immediately post-exercise to both groups. For the VR intervention group, system usability will be assessed using the System Usability Scale (SUS) [20, 21], a 10-item questionnaire administered immediately post-exercise to measure ease of use, comfort and perceived immersion with the VR technology.

Vital signs monitoring will be performed before, during (every minute) and after exercise using standardized equipment: pulse oximetry for oxygen saturation (SpO₂), automated sphygmomanometer for systolic and diastolic blood pressure (BP) and continuous heart rate monitoring via pulse oximeter and ECG. Continuous 12-lead ECG monitoring via bedside cardiac monitor will be performed during all exercise sessions for safety surveillance. Continuous ECG waveforms during the exercise session will not be archived. Only ECG strips corresponding to detected clinically significant arrhythmias (atrial fibrillation, ≥ 6 consecutive ventricular ectopic beats, sustained ventricular tachycardia** > **3 beats) or ischemic changes (≥ 1 mm ST-segment deviation from baseline) will be saved for post-hoc review by a blinded cardiologist.

Perceived exertion will be assessed using the Modified Borg Rating of Perceived Exertion Scale (0–10), administered at baseline, every minute during exercise and post-exercise to monitor exercise intensity and participant tolerance. All outcome data will be recorded in real-time on standardized forms during the exercise session to minimize measurement error and recall bias. Post-exercise questionnaires (PACES and SUS) will be administered while participant experience remains fresh, typically 5–10 min after exercise completion. All data will be entered into the secure REDCap database with mandatory quality checks for completeness, consistency and integrity before database lock.

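### In-session encouragement by the unblinded physiotherapist is an adherence strategy, but nothing makes it equal between arms although the primary outcome is time to interruption

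*Protocol article*

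**What the plan says.** - **Endpoint.** Under Outcomes {16}: "The primary endpoint is effective exercise time (minutes), defined as total session duration until interruption due to physical limitations or symptoms". The list of participant-initiated discontinuations in {15b} lets a participant stop for discomfort, inability to continue or any other reason.
- **Encouragement.** Under {15c}, "continuous physiotherapist supervision provides real-time guidance, encouragement and safety oversight". The same section says that "adherence encompasses participant attendance and protocol completion", and qualifies this by safety, comfort and the participant's sense of control.
- **Blinding.** Under Blinding limitations {24a}, "participants and the physiotherapist cannot be blinded". The Harms section adds: "The supervising physiotherapist has authority to terminate the exercise session immediately if any safety concern arises".
- **Safeguards.** Measures to minimize bias ({24a}) lists standardised verbal instructions, a blinded analyst and this: "Vital signs and exercise duration will be recorded using calibrated, automated monitoring equipment in real-time". The control-group description promises the same physiotherapist supervision. Section {24b} says that participants and physiotherapist will not be told the hypotheses. The discontinuation criteria are stated to apply identically to both groups.
- **Recording.** Section {25a} has the supervising physiotherapist collect the data on case report forms. Footnote k of the participant timeline says that vital signs, exertion ratings and observations are "recorded by physiotherapist on paper CRF during exercise".

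**The concern.** How long a hospitalised patient keeps pedalling depends partly on willingness, and the plan itself uses encouragement to promote completion of the session. Completion is also the ceiling of the primary outcome. The adherence strategy and the outcome measurement therefore act on the same quantity, and the person applying the strategy knows the arm.

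If prompting is warmer, more frequent or better timed in one arm, mean exercise time differs for a reason unrelated to immersion. The direction cannot be predicted: a physiotherapist might urge VR participants on, or might compensate controls for the missing headset. In either case the protocol's claim that any difference can be attributed to VR itself would be weakened, and nothing at the analysis stage could repair it.

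**Working it through.** **Step 1. Does any stated safeguard fix the encouragement?**

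| Safeguard | Where | What it fixes | What it leaves open |
|---|---|---|---|
| Standardised verbal instructions | Measures to minimize bias {24a} | How the task is explained | Prompts given while pedalling |
| Same supervision in both arms | Control-group description {15a} | Who supervises | What is said, and when |
| Hypotheses withheld | {24b} | One motive for uneven prompting | Habit, or expectation from seeing the headset |
| Identical stopping criteria | {15b} | Mandatory stops | Voluntary stops before those limits |
| Automated timing | {24a} | Error in measuring time | A real change in time caused by prompting |
| Blinded analyst | {24a}, {24b} | Choices made in analysis | Anything that happened in the session |

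None makes the encouragement equal between arms.

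**Step 2. How large could the effect be?** The plan gives no figure for encouragement and no SD for exercise time. Its only usable inputs are 30 per group and d = 0.65 (Sample size {19}) and the 3-min block ({15a}). The rest is assumed: encouragement keeps 10% to 20% of one arm (3 to 6 of 30) going for one more block, has no such effect in the other arm, and the SD is 3 to 5 min. Time is counted as pedalling time.

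Shift in the arm mean = (number affected / 30) × 3 min:
- 3/30 × 3 = 0.3 min
- 6/30 × 3 = 0.6 min

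Planned effect in minutes = 0.65 × SD:

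| Assumed SD | Planned effect | 0.3 min as share | 0.6 min as share |
|---|---|---|---|
| 3 min | 1.95 min | 15% | 31% |
| 4 min | 2.60 min | 12% | 23% |
| 5 min | 3.25 min | 9% | 18% |

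In SD units the shift runs from 0.3/5 = 0.06 to 0.6/3 = 0.20.

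**Step 3. Effect on the false-positive rate.** Take no true VR effect, 30 per group, a two-sided 5% t test and a constant shift b in SD units. The noncentrality is b × √(30/2). For b = 0.1 it is 0.39, and the rejection rate is about 7%. For b = 0.2 it is 0.77, and the rate is about 12%. The assumed scenarios therefore run from slightly above 5% to about 12%.

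**Step 4. Where does the recorded time come from?** Section {25a} names devices for oxygen saturation, blood pressure, heart rate and ECG, but none for exercise time. The control-group description mentions an ergometer display showing time, but lists it among the differences from the VR group. No timing source common to both arms is named.

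**The case against.** The best defence is that encouragement is part of routine supervision, is given in both arms, and is surrounded by safeguards. The article names unequal clinician attention as something the design avoids, delivery follows institutional protocols, and the physiotherapist is not told the hypotheses. The session is also capped, with identical mandatory stops, so urging cannot permissibly extend it past those limits. Exact prompts are the kind of detail that a journal article may leave to the full protocol.

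Much of this stands. The cap and the stopping criteria limit how far encouragement can act, and withholding the hypotheses removes one motive. But the article affirmatively adopts encouragement as a strategy, and its listed bias measures do not extend to it. Naming unequal attention as avoided is not a mechanism for avoiding it.

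Two stronger readings are tempting, and the documents do not support either.

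- *That the plan favours the VR arm.* The encouragement sentence is not limited to one arm and no difference is planned. The retention section ({25b}) says VR will be presented as an innovative tool, but that concerns what participants hear, not how the physiotherapist prompts. Nor is adherence defined purely as maximising time, given the qualification about safety, comfort and control.
- *That automated recording is contradicted by hand recording.* A device reading can be copied onto a form, and the timeline footnotes already pair the two for vital signs: automated monitors in footnote e, paper forms in footnote k. Footnote k does not list duration, the ergometer is the same in both arms, and {27b} says duration is measured continuously. What is left is an unnamed timing source.

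**Conclusion.** The concern holds as an uncontrolled risk to the primary outcome, not as a demonstrated bias. It rests on three statements in the plan: encouragement is used to promote completion, the person giving it is unblinded, and the outcome is a partly voluntary time to interruption. The stated safeguards do not equalise what is said or when.

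The size is unknown. A shift of 0.3 to 0.6 min, or 9% to 31% of the planned effect, follows only if the assumed number of participants, the one extra block, the one-sided influence and the SD range are accepted. On those assumptions the bias is modest, but it would act in one direction and could not be removed afterwards. The timing source is a secondary matter of clarity. The change is worth making because it is cheap.

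**What to change.** **Main change.** In {15c} and in Measures to minimize bias ({24a}), state that encouragement follows a fixed script, with the same words at the same elapsed times in both arms. State also that safety communication is unrestricted and that the stopping criteria are unchanged.

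**Secondary change.** In {25a} and the timeline footnote on total exercise time, name one device clock, used in both arms, from which pedalling start and stop are read and entered on the case report form. The ergometer console is a candidate if the physiotherapist can read it during VR sessions, which the sponsor should confirm. If no common device is available, remove exercise duration from the claim of automated recording.

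**Cost.** A one-page script and two form fields, with no extra staff. The physiotherapist loses a little freedom to motivate participants. Recruitment was due to start on 10 November 2025 and to run to 10 November 2026, so the change may come mid-trial. It should then go through the amendment procedure in {31}, with its start date recorded. Allocation in blocks of 4 should keep the arms nearly balanced before and after that date.
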